### Experimental Protocol

Participants will attend 6 experimental sessions, as outlined in Figure 1. Session 1 will be conducted at the Clinical Research and Imaging Centre ([name] and Partners, South Australian Health and Medical Research Institute) where magnetic resonance imaging (MRI) sequences will be performed to obtain structural, diffusion, and functional images. Session 2 will be conducted within 5 days of the initial MRI scan at the University of South Australia, City East Campus, Clinical Trials Facility. Participants will be encouraged to attend this experimental session with a supportive family member, friend, or carer. In this session participants will undergo baseline neurophysiological and behavioral outcome assessments and will be provided with a home tDCS kit (NeuroConn DC-Stimulator Mobile, NeuroConn GmbH, Ilmenau, Germany). Participants and their support person will be trained in the use of the home tDCS, iPad, and the Graded Repetitive Arm Supplementary Program (GRASP) exercises. In addition, information sheets will be provided for the use of the home tDCS equipment and the iPad. This information will detail the correct use of equipment, including locating the correct spot for tDCS electrode position, which will be marked on the scalp with a permanent marker. To facilitate training, the first of 14 treatments will be undertaken at the Clinical Trials Facility under the supervision of a research staff member. An iPad will be provided to each participant to facilitate monitoring of home tDCS using a telehealth platform. Each iPad will be preloaded with a videoconferencing platform (Skype), allowing the research staff to monitor the tDCS set-up and use across the intervention period.

Experimental sessions 3, 5, and 6 are respectively performed immediately, 1 month and 3 months following the final home tDCS treatment. During these sessions, participants will undergo neurophysiological and behavioral outcome assessments. Experimental session 4 is a follow-up MRI session and will occur within 5 days of the final tDCS treatment.

Inclusion criteriaAged ≥18 years of ageAt least 6 months after the first ever stroke with motor impairmentMeasurable impairment of the upper limb (Fugl-Meyer upper extremity of <62 out of 66)Supportive family, friends, or carers willing to actively assist and motivate across the 2-week interventionActive wrist extension of, at least, 5°Active index finger flexion of, at least, 10°Modified Ashworth scores of <4 for the affected elbow, wrist, and metacarpal phalangeal joints

Exclusion criteriaTranscranial magnetic stimulation and transcranial direct current stimulation safety exclusion criteria as per international guidelines [25]Contraindications for magnetic resonance imagingSelf-reported neglect, apraxia, or shoulder pain (>4 out of 10 on pain visual analog scale) that would affect the ability to undertake a 1-hour upper limb exercise program.Language or cognitive impairment that would limit the ability to communicate with the research team by videoconferenceParticipation in a concurrent research study or clinical program for upper limb rehabilitation.

**Figure 1 figure1:**
[figure not shown]
The schematic diagram of the experimental sessions. tDCS: transcranial direct current stimulation; EEG: electroencephalography; TMS: transcranial magnetic stimulation; ARAT: action research arm test; FM-UE: Fugl-Meyer Upper Extremity; GRASP: Graded Repetitive Arm Supplementary Program; MRI: magnetic resonance imaging; FLAIR: fluid-attenuated inversion recovery; DTI: diffusion tensor imaging; fMRI: functional magnetic resonance imaging.

### Intervention

#### Graded Repetitive Arm Supplementary Program

All participants will be provided with a home exercise program using the GRASP [26]. The GRASP protocol consists of a booklet with detailed descriptions of multiple exercises for strength, range of motion, fine motor, and goal-directed activities targeting the upper limb. The provided kit includes all required equipment to perform the exercise program. The GRASP protocol is a self-administered program with program levels (grades 1-3) individualized by a qualified occupational therapist, based on the level of impairment of the upper limb. The upper limb exercises will be performed for 1 hour per day over a 2-week period (14 sessions).

#### Transcranial Direct Current Stimulation

Participants will also be provided with a home tDCS kit, which will be preprogrammed for 14 sessions of active or sham stimulation using a study code to facilitate research staff blinding. Participants will be unable to modify, or observe, any settings of the home tDCS devices. To initiate stimulation, participants will simply position electrodes on the head and press the start button. Those randomized to the “active” arm of the study will receive tDCS while simultaneously performing the GRASP exercises. TDCS will be delivered for 20 minutes and occur at the same time that a participant is undertaking the 1-hour GRASP program. Therefore, the initial 20 minutes of the intervention will involve both tDCS and the GRASP, with the remaining 40 minutes involving only GRASP exercises. The electrodes will be positioned with the anode over the ipsilesional M1 and cathode over the contralateral supraorbital region. TDCS will be applied at an intensity of 1 mA for 20 minutes daily for 2 weeks (total of 14 sessions) at home. Stimulation will be ramped up from 0 mA to 1 mA over the first 30 seconds and down from 1 mA to 0 mA over the final 30 seconds.

Participants randomized to the “sham” arm of the study will receive sham tDCS while undertaking the 1-hour individualized GRASP exercises. Electrodes will be positioned in the same location as the active tDCS group. Sham tDCS mimics the sensation of stimulation without changing cortical excitability. The protocol for sham tDCS will ramp the current up from 0 mA to 1 mA over the first 30 seconds before ceasing for the following 19 minutes and 30 seconds. This approach has been shown to provide an effective sham stimulation [27].

#### Compliance Monitoring

Several strategies will be used to monitor protocol compliance and ensure the correct use of home tDCS (for a summary see Textbox 3). The number of completed tDCS sessions and daily duration of GRASP will be recorded in a treatment diary.

#### Adverse Events and Assessment of Blinding

At the completion of the 2-week tDCS intervention, participants will be asked to complete a questionnaire to identify any adverse events and establish whether participant blinding was successful. In accordance with current recommendations [28], we will ask participants to rate on a scale of 1-4 (1, absent; 2, mild; 3, moderate; 4, severe) the presence of the following symptoms: headache, neck pain, scalp pain, tingling, itching, burning sensations, skin redness, sleepiness, trouble concentrating, acute mood change, and other symptoms. In addition, we will ask participants to what extent they believe the reported symptoms were related to using tDCS (1, none; 2, remote; 3, possible; 4, probable; 5, definite). Furthermore, we will ask participants to indicate whether they believe they received active stimulation (yes or no) to determine the effectiveness of blinding.

### Outcome Measures

Textboxes 4 and 5 summarize the independent and dependent variables to address the primary research question for this study. Participant demographics and clinical characteristics including age, gender, handedness [29], and time since stroke will be recorded and compared between the active and sham groups.

#### Assessments of Upper Limb Function

The primary outcome measure for this study is a change in upper limb impairment as measured with the Fugl-Meyer upper extremity (FM-UE) assessment. The FM-UE is a commonly used, validated, and reliable measure of sensorimotor impairment [30]. The FM-UE is considered as one of the most comprehensive quantitative measures of motor impairment following stroke.

In addition, upper limb function will be assessed with the action research arm test (ARAT) and grip strength. The ARAT is a valid and reliable measure of hemiplegic upper limb function [31]; it provides a quantitative measure of upper limb function for domains of grip, grasp, pinch, and gross arm movement. Grip strength is associated with motor cortical output and motor recovery [32]. We will measure grip strength using a hand dynamometer (SH5001 Saehan Hydraulic Hand Dynamometer, Saehan Co, Masan, Korea). The best (maximal) grip of 3 attempts will be recorded.

Strategies to facilitate protocol compliance.*Support person*: A support person will attend training for home transcranial direct current stimulation (tDCS) and graded repetitive arm supplementary program (GRASP) exercises to assist, and motivate, participants as required across the intervention.*Initial treatment under supervision*: The first treatment will be completed under supervision to ensure the correct use of tDCS.*TDCS electrode position marked on scalp*: The correct positioning of tDCS electrodes will be marked on the scalp with a permanent marker to facilitate home application.*Information sheet*: Step-by-step instructions for the use of the home stimulator.*Videoconference*: In real time, confirm correct tDCS usage, provide motivation, and progress individual exercise programs or GRASP grade. Videoconferences will occur every second day at a minimum and more frequently if required.*Exercise diary*: Record daily completion of tDCS and GRASP. Includes recording duration of GRASP therapy, motivation, fatigue, and perceived exercise difficulty.

Dependent variablesPrimaryChange in upper limb impairment (Fugl-Meyer Upper Extremity)SecondaryChange in the upper limb function (action research arm test)Change in the upper limb strength (grip strength)Change in the corticospinal excitability obtained from motor-evoked potential amplitude

Independent variablesFunctional connectivityTask functional magnetic resonance imagingResting state functional magnetic resonance imagingElectroencephalographyStructural connectivityFractional anisotropy index of the corticospinal tract obtained from diffusion tensor imagingAnatomicalLesion volumeDemographics and clinical characteristicsAgeGenderTime since strokeAffected hemisphere based on hand dominance

Outcome assessors will be blind to group allocation and have completed training for FM-UE and ARAT assessments through the University of California Irvine. Training outcome assessors with this approach has been shown to improve accuracy and reduce variance of the FM-UE and ARAT [33,34].

### Neurophysiological Testing

#### Electroencephalography

Functional connectivity between brain regions will be assessed with high-density EEG. Three minutes of EEG will be acquired using an ASA-lab EEG system (ANT Neuro, Enschede, the Netherlands). Participants will be fitted with an ANT Waveguard cap with 64 sintered Ag-AgCl monopolar electrodes in standard 10-10 positions. Signals will be sampled at 2048 Hz, amplified 20X, filtered (high pass, DC; low pass, 553 Hz) and online referenced to CPz. During data recording, participants will be seated in a comfortable chair in a quiet room. Standardized instructions will be delivered to each participant asking them to relax during the 3 minutes of data recording, keep their eyes open, refrain from speaking or moving, maintain their gaze toward a fixation point straight ahead at eye level and not actively engage in any cognitive or mental tasks. Impedance will be kept <5 kΩ while recording.

Artifact rejection will be performed prior to analysis using independent component analysis. Nonphysiological artifacts will be identified using an automated and objective method to remove assessor bias [35]. Preprocessed data of participants with a right hemisphere lesion will then be flipped about the midline so that all lesions appear in the left hemisphere. Functional connectivity between electrodes will be determined using the debiased weighted phase lag index, which is a conservative estimate of connectivity based on phase consistency and biasing against zero phase lag relationships, limiting the detection of spurious measures of connectivity [36]. Regions of interest will include a seed approximating the ipsilesional M1 (C3) and clusters of electrodes approximating the ipsilesional premotor (F5, F3, FC5, and FC3), ipsilesional parietal (CP3, CP5, P3, and P5), and contralesional M1 (C4). Frequency bands of interest are the alpha band (8-15 Hz) and beta band (16-31 Hz) as they are associated with sensorimotor function [20,37,38]. For a given frequency, a debiased weighted phase lag index value of 1 indicates maximal phase coupling, whereas a value of 0 indicates no phase coupling. Connectivity analyses will be performed in MATLAB 9.2.0 (MathWorks, Inc) using both EEGLAB [39] and FieldTrip toolboxes [40].

#### Transcranial Magnetic Stimulation

Single-pulse transcranial magnetic stimulation will be used to quantify corticomotor excitability of the ipsilesional M1. Monophasic (posterior to anterior current flow) transcranial magnetic stimulation pulses will be delivered with a Magstim 200 stimulator (Magstim, Whitland, United Kingdom) via a figure-of-eight coil (70-mm wing diameter). The coil will be placed tangentially over the scalp with the handle pointing 45° posterolateral. Surface electromyography will be used to record motor-evoked potentials (MEPs) from the first dorsal interosseous muscle of the paretic hand with electrodes positioned in a belly-tendon montage. Suprathreshold stimuli will be delivered over the ipsilesional hemisphere to identify the optimal position for evoking an MEP from the first dorsal interosseous muscle of the paretic hand. For participants where MEPs cannot be evoked even at maximal stimulator output as a result of the stroke, we will document that a measure of corticospinal excitability was not obtainable at that experimental session. For participants where MEPs can be evoked, the optimal site will be marked on the scalp using a felt-tip marker to ensure consistent coil placement during subsequent data collection. Resting motor threshold will then be determined and is defined as the minimum stimulus intensity required to evoke an MEP of at least 50 μV in at least 5 of 10 consecutive trials. Thirty stimuli, not contaminated by pre-stimulus electromyography, will then be obtained at 120% resting motor threshold (interstimulus interval 4.5-5.5 sec) with the average, peak-to-peak amplitude, determined as a reliable measure of corticospinal excitability [41].

#### Magnetic Resonance Imaging

MRI will be performed at the Clinical Research and Imaging Centre located at the South Australian Health and Medical Research Institute with a Siemens 3T MAGNETOM Skyra scanner (Siemens, Erlangen, Germany). Standard MRI safety screening will be performed to ensure included participants are safe for MRI. At the preintervention MRI session, the imaging protocol will have a duration of 45 minutes and include T1 MPRAGE and T2-weighted fluid-attenuated inversion recovery images, diffusion tensor imaging, resting state, and task functional MRI (fMRI). At the postintervention MRI session, the imaging protocol will have a duration of 30 minutes and include T1-weighted images, resting state fMRI, and task fMRI.

The imaging protocols are as follows: T1-weighted images (MPRAGE, voxel 1 mm × 1 mm × 1 mm, repetition time (TR)=2300 ms, echo time (TE)=2.98 ms, flip angle=9°), T2-weighted fluid-attenuated inversion recovery images (voxel 1 mm × 1 mm × 1 mm, TR=5000 ms, TE=393 ms), diffusion MRI (voxel 2 mm × 2 mm × 2 mm, TR=4200 ms, b-value=0 and 2000 s mm), resting state fMRI (voxel 2.4 mm × 2.4 mm × 2.4 mm, TR=735 ms, TE=36 ms, 2 repeats of 6-min duration, 490 measurements for each), and task fMRI (voxel 2 mm × 2 mm × 2.5 mm, TR=3000 ms, TE=30 ms, 4.44-min duration). During the task fMRI, participants will be presented with a visual cue to squeeze a stress ball in their paretic or nonparetic hand, with blocks alternating every 30 seconds and repeated 4 times per hand.

Preprocessing and statistical analyses of MRI data will be carried out using tools from the FMRIB Software Library [42]. For all voxel-wise analyses, images from participants with lesions of the right hemisphere will be flipped about the midline after registration to standard space so that all lesions appear in the left hemisphere. fMRI data will be preprocessed and analyzed using the FMRIB Expert Analysis Tool [43]. Preprocessing steps will include high-pass temporal filtering at 0.01 Hz, spatial smoothing, motion correction, and removal of nonbrain tissue. Task fMRI data will be analyzed with a boxcar regressor, which will model task and rest blocks for first-level statistical maps for each participant. Higher level mixed-effects analysis will then be run using FMRIB Local Analysis of Mixed Effects [43] to test correlations with improvement in clinical scores and compare activation maps across groups.

For resting state fMRI, nuisance regressors of no-interest (cerebrospinal fluid, white matter, head motion, and physiological noise) will be modeled and removed. We will then calculate the mean time course of the blood-oxygenation level dependent signal in all voxels of the ipsilesional M1 region of interest. This time series will then be entered separately as an explanatory variable in the general linear model to determine for each participant the voxels where blood-oxygenation level dependent signal is temporally correlated with the ipsilesional M1. Connectivity between the ipsilesional M1 and other regions of interest (contralesional M1, ipsilesional dorsal premotor cortex, ipsilesional ventral premotor cortex, ipsilesional supplementary motor area, and ipsilesional posterior parietal cortex) will be determined with a Pearson’s correlation coefficient. Connectivity of the ipsilesional M1 will be compared before and after tDCS with a general linear model.

Structural connectivity will be analyzed with the FMRIB Diffusion Toolbox [44]. For each participant, the mean fractional anisotropy (FA) of the posterior limb of the internal capsule will be determined. An asymmetry index will be calculated as follows: FA = (FA–FA) / (FA+FA).

Lesion volume will be defined by manually tracing the lesion in FLS view. Lesions will be traced from each participant’s T1-weighted image using the coregistered T2-weighted image as a reference for lesion extension.

### Statistical Analysis

Normality of data will be confirmed using Shapiro-Wilk normality tests. Where required, data will be normalized using transformations or nonparametric statistics applied. Participants’ demographics and clinical characteristics will be compared between active and sham groups. The effect of the intervention on behavioral and neurophysiological outcome measures will be investigated with a 2 Group (active, sham) × 4 Time Point (Baseline, Postintervention, 1-Month Follow-up, 3-Month Follow-up) repeated measures analysis of variance. Independent variables (Textbox 5) will be correlated with the primary outcome measure for response to anodal tDCS (change in upper limb impairment measured with the UE-FM). Where appropriate, regression models will be generated using those independent variables significantly correlated with change in upper limb impairment to identify a combination of measures associated with response to anodal tDCS. Any regression models generated will be compared using the Bayesian information criteria [45]. Where appropriate, the predictive capacity of the generated model will be investigated using a leave-one-out cross-validation. This cross-validation will be performed on participants allocated to both active and sham treatment groups to demonstrate that the predictive model is specific to the stimulation group. Statistical testing will be performed using SPSS (IBM Co, version 24.0) and significance level will be *P* ≤.05.

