**Methods:**

This study is a double blind, randomized controlled trial (RCT), with two parallel groups. A total of 68 participants with first ever ischemic stroke with motor impairment will undertake a two week (14 session) treatment for upper limb function (Graded Repetitive Arm Supplementary Program; GRASP). Participants will be randomized 2:1 to active:sham treatment groups. Those in the active treatment group will receive anodal transcranial direct current stimulation to the ipsilesional motor cortex at the start of each GRASP session. Those allocated to the sham treatment group will receive sham transcranial direct current stimulation. Behavioural assessments of upper limb function will be performed at baseline, post treatment, 1 month follow-up and 3 months follow-up. Neurophysiological assessments will include magnetic resonance imaging (MRI), electroencephalography (EEG) and transcranial magnetic stimulation (TMS) and will be performed at baseline, post treatment, 1 month follow-up (EEG and TMS only) and 3 months follow-up (EEG and TMS only).

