### Sample Size

Our primary aim is to determine the characteristics of the sensorimotor network at baseline that may predict the responsiveness to anodal tDCS in people with stroke. Therefore, our sample size calculation was based on pilot data of 10 people with stroke where we observed a medium to large effect size (r=0.56) for a correlation between baseline high beta frequency connectivity and change in cortical excitability following anodal tDCS [21]. Using this effect size with alpha set at .05 and power of 95%, we determined a total sample of 47 would be required. However, we will aim to recruit a total sample of 68, given our methodological approach of using unequal group allocation (additional 12%) and the nature of the home-based treatment with a longer follow-up study period (allowing 30% dropout). This will result in 45 participants in the active treatment group and 23 participants in the control group.

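### The four-visit repeated-measures ANOVA for active versus sham would conventionally analyse only complete cases, about 47 of 68 at the planned 30% dropout, and so set aside post-treatment data already observed

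*Protocol article*

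**What the plan says.** The Statistical Analysis section of the protocol article names one model for the group effect: "The effect of the intervention on behavioral and neurophysiological outcome measures will be investigated with a 2 Group (active, sham") crossed with "Time Point (Baseline, Postintervention, 1-Month Follow-up, 3-Month Follow-up) repeated measures analysis of variance". The software is SPSS 24.0.

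The Sample Size section inflates the sample partly for "the nature of the home-based treatment with a longer follow-up study period (allowing 30% dropout"), giving 45 active and 23 sham participants.

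Two other places bear on which data are complete:

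- The Transcranial Magnetic Stimulation section says that where no motor-evoked potential (MEP) can be evoked because of the stroke, "we will document that a measure of corticospinal excitability was not obtainable at that experimental session". MEP amplitude is a secondary dependent variable.
- The Abstract counts MRI among the neurophysiological assessments. It limits the later visits to "1 month follow-up (EEG and TMS only) and 3 months follow-up (EEG and TMS only"), so MRI exists only at baseline and post treatment.

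The Introduction makes active versus sham a secondary objective. The article does not say how incomplete visits enter the ANOVA.

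**The concern.** Conventional repeated-measures ANOVA needs a full row of visits for each participant and deletes the rest. The article combines that method with an expected 30% dropout, which it attributes in part to the length of follow-up. Two things are at stake.

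- **Precision.** A value observed at the post-treatment visit is discarded if the same person later misses month 1 or month 3.
- **Selection.** The analysed set is those who stayed throughout. If leaving is related to response differently in the two arms, the completer contrast is biased. Inflating the sample replaces numbers but does not remove selection.

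The comparison is secondary, but it uses the primary outcome measure (FM-UE). The Study Design section gives showing a group-level effect as one of two reasons for having a sham arm.

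**Working it through.** **Inputs from the article:** 68 participants (45 active, 23 sham), 30% dropout, 12% inflation for unequal allocation, base sample 47, and four visits in the model.

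**Assumed, because the article gives nothing for the group contrast:** SD of FM-UE gain 4.5 points, true effect 3 points, the timing and mechanism of dropout, and between-visit correlation 0.5 to 0.8.

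**1. The plan's total.** 47 × 1.12 × 1.30 = 68.4, so 68 is reproduced. The base of 47 was set for a correlation (r=0.56), not for active versus sham. (Two-sided Fisher z for r=0.56 at 95% power gives 36, not 47. That is a separate matter and does not affect this point.)

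**2. Complete cases.** 68 × 0.70 = 47.6; 45 × 0.70 = 31.5 active; 23 × 0.70 = 16.1 sham. About 31 and 16 remain.

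**3. Largest loss of precision.** The SE of a difference in means, in SD units, is √(1/n₁ + 1/n₂).

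- All 68: √(1/45 + 1/23) = 0.256
- Completers: √(1/31 + 1/16) = 0.308, which is 20% larger

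**4. Post-treatment visit, by timing of dropout.** If a share d of the 68 leaves before the post-treatment visit and 30% leave in all, the completer SE relative to all available post-treatment data is √((1 − d)/0.70).

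| Lost before the post-treatment visit | SE ratio | Penalty |
|---|---|---|
| 0% | √(1.00/0.70) = 1.195 | 20% |
| 10% | √(0.90/0.70) = 1.134 | 13% |
| 20% | √(0.80/0.70) = 1.069 | 7% |
| 30% | √(0.70/0.70) = 1.000 | 0% |

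In the 10% case, 68 × 0.90 = 61 people have post-treatment data. With the assumed SD and effect and random dropout, simulated power is about 69% with all available data and 57% with completers.

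**5. Bias at the post-treatment visit.** These are simulations with 10% lost before the visit and the rest after it. Dropout after the visit depends on gain in the active arm only, and the slope is the strength of that dependence per SD of gain. Each range covers simulations set up slightly differently.

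| Slope | Bias on a true effect of 3 points | Type I error under no effect |
|---|---|---|
| 0.5 | about 0.5 | 6% to 7% |
| 1 | about 0.9 | 10% to 13% |
| 2 | about 1.3 to 1.4 | 19% to 21% |

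When dropout is random, or depends on gain equally in both arms, the bias is about zero.

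**6. What a likelihood model recovers at month 3.** In SD units, under random dropout after the post-treatment visit, the SE is 0.256 with no dropout, about 0.308 for completers, and 0.275 to 0.297 for a model using all available visits (correlation 0.8 to 0.5). Only part of the loss comes back. With dropout related to response in the active arm only, completer bias at month 3 is +0.13 to +0.20 SD on a true effect of 0.5 SD. The likelihood estimate has about zero bias in these missing-at-random cases.

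**The case against.** **Listwise deletion is not stated.** It is a property of the conventional procedure, and the article does not rule out imputation. A fuller analysis plan might address incomplete visits. That is fair, so the point concerns the method the article names and its fit with the article's own dropout figure, not absent detail.

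**The loss may be small.** If people leave mainly during the two weeks of home treatment, few post-treatment values are discarded and the penalty at that visit approaches zero. This stands, and it is why a range is given.

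**The bias needs a particular mechanism.** Participants are blinded, and similar dropout in both arms gives about zero bias. This also stands. A reader might infer that the completer result will be biased, or take the error rate near 20% as typical. The documents support neither, because that figure needs strong response-related dropout in one arm only.

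**MRI.** A reader might infer that having MRI at only two visits weakens the active-versus-sham comparison. It cannot. The listed dependent variables are FM-UE, ARAT, grip strength and MEP amplitude, and the Magnetic Resonance Imaging section gives MRI its own group and pre/post analyses. What remains is loose wording: read with the Abstract, the term for neurophysiological outcomes in the ANOVA sentence would take in MRI, which cannot enter a four-visit model.

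**Baseline as a level of time.** The group-by-time interaction already compares change from baseline. Adjusting for baseline instead multiplies the SE by √((1 + ρ)/2), a 5% reduction at an assumed ρ of 0.8. The gain is real but small.

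**It is secondary.** This is correct. The primary correlation analysis does not use this ANOVA.

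**Conclusion.** The point holds in limited form. As named, the ANOVA would conventionally use about 47 of 68 participants at the planned dropout, with about 16 in the sham arm, and would drop post-treatment values from people who miss a later visit. The cost in precision at that visit is 0% to 20% of the SE, depending on timing that the article does not give. Bias is possible rather than shown. In the assumed cases of active-arm-only dependence it is about 0.5 to 1.4 points on an effect of 3, with type I error about 6% to 21%. The SD, effect, correlations and dropout mechanisms are all assumptions.

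The clearest case in the document is MEP amplitude. The article expects sessions with no obtainable MEP because of the stroke, and one such session removes that person from a complete-case ANOVA. These values are missing because they are low, so a missing-at-random model does not correct the problem either.

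The change should be made. It affects the secondary efficacy question and leaves the primary biomarker analysis untouched.

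**What to change.** 1. For FM-UE, ARAT, grip strength and the EEG and TMS outcomes, replace the ANOVA with a linear mixed model for repeated measures (SPSS MIXED). Include every randomised participant with any follow-up value. Use the three follow-up values as outcomes; baseline value, group, visit and group × visit as fixed effects; and an unstructured covariance. Read the group contrast at each visit from this model.
2. State separately how unobtainable MEPs are analysed.
3. Limit the four-visit model in the Statistical Analysis section to outcomes measured at four visits, and refer MRI to the analyses already described in the Magnetic Resonance Imaging section.

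The cost is a change of analysis wording and slightly more analysis work in the software already named. The model relies on missing at random. Its main gains are at the earlier visits and in protection against bias under that assumption; at month 3 it recovers only part of the lost precision.
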